### Measures

The PIPP is a seven-item multidimensional (composite) measure of pain, largely used to assess acute pain in infants [11] and extensively validated for both preterm and term newborns [22]. Items are empirically and theoretically derived and are categorised as: contextual ((GA) and behavioural state (BS)), physiological (heart rate and oxygen saturation) and behavioural (facial actions). Numeric scores, reflecting baseline changes and based on an empirically 4-point scale (0, 1, 2, and 3), are provided for physiological and behavioural items. Conversely, the contextual items (GA and BS) have a reversed score (3, 2, 1, and 0) accounting for physiological differences related to prematurity. The maximum PIPP score is 21 for infants < 28 weeks GA and 18 for full-term newborns.

Considering LOS, according to international guidelines, well-determined discharge parameters are required and listed as follows: coordinated breathing, swallowing and sucking while feeding; stability of cardiorespiratory function; sustained weight gain and body heat at room temperature [23].

Regarding NICU costs, costs per day are calculated according to local authorities, multiplied by the days of hospitalisation. Costs are estimated in euros per day.

### Statistical analysis

According to Stevens *et al*. [11] the mean PIPP score for a painful procedure is 12.9 (standard deviation (SD), 3.4) and 6.0 (SD, 2.7) for a non-painful procedure. For a heel stick, the mean score is 10.3 (SD, 4.5) and 6.3 (SD, 3.2) for a simulated handling. However, as there is a lack of clinical trials in complementary medicine and/or manual disciplines, the sample size is computed considering an effect size (f) of 0.30, a statistical power of 0.80 and an α-level equal to 0.05 to produce a sample size of 37 per group. To prevent loss of power, the sample size is increased up to 40 subjects per group (total sample N = 120).

The primary analysis of the present clinical trial will be conducted according to per-protocol principle and intention-to-treat. Missing data will be handled using the last observation carried forward imputation technique. Arithmetic means and SD as well as median, percentage and range will be used to describe the general characteristics of the study population. Univariate statistical tests, Student’s *t*-test, analysis of variance (ANOVA) and chi square test, will be performed to compare the study groups and control group at the baseline. A linear mixed effect model will be used to evaluate the PIPP score across groups. Data will be analysed within and between the three study groups. Furthermore, a linear regression model will be applied to study the independent effect of OMT on primary and secondary endpoints between OMT groups A and B. Two-tailed *P*-values of less than 0.05 are considered to indicate statistical difference. To describe imbalances between groups, mean or relative risk with 95% CI will be used. Effect sizes will be computed stratifying by gestational age. R statistical programme (Vienna, Austria) will be used for data analysis [24].

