**Methods/design:**

A three-armed single blinded placebo-control randomised controlled trial protocol has been designed to primarily evaluate the extent to which OMT is effective in reducing pain in preterms. One hundred and twenty newborns will be enrolled from one tertiary neonatal intensive care unit in central Italy and randomised in three groups: study, sham and control. The study group will be further prospectively randomised in two subgroups: experienced osteopaths and students. All preterms will receive standard medical care. Osteopathic treatment will be applied to the study group only whilst ‘soft touch’ will be administer to the sham group only. Newborns will undergo manual sessions once a week for the entire period of hospitalisation. Blinding will be assured for neonatal staff and outcome assessor. Primary outcome will be the mean difference in baseline score changes of PIPP questionnaire between discharge and entry among the three groups. Secondary outcomes will be: mean difference in length of stay and costs between groups. Statistical analyses will use per-protocol analysis method. Missing data will be handled using last observation carried forward imputation technique.

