## Methods/design

The current protocol is designed for a single blinded placebo-control randomised controlled trial (RCT) aiming at evaluating the extent to which OMT is effective in reducing pain in preterms. Secondary objectives will be reduction of LOS and cost-effectiveness.

From 5 May 2014 to 30 September 2015 newborns will be enrolled in the study at one tertiary neonatal ICU (NICU). Newborns will enter and be randomised only after parents or guardians have given written informed consent.

Infants who are admitted to the NICU will be eligible for inclusion. Inclusion criteria are: being born in Pescara’s hospital, having a gestational age (GA) between 29 and 37 weeks, being of either gender and without clinical and/or congenital complications. Exclusion criteria will be applied as follows: lack of guardian consent, having a gestational age > 37 weeks, being a newborn with HIV and from HIV seropositive/drug-addicted mother, being transferred to/from other hospital, the presence of any congenital or genetical disease, neoplasms, neurological, cardiovascular, urinary, haematological abnormalities, proven or suspected necrotising enterocolitis or abdominal obstruction, birth trauma, surgical patients, pneumoperitoneum, atelectasis, respiratory distress.

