### Osteopathic procedure

Osteopathic care includes an initial structural evaluation and a final treatment. The structural evaluation is carried out with the newborn lying down in bed and is aimed at diagnosing somatic dysfunctions [19]. The osteopathic manipulative treatment includes the application of a range of manipulative techniques aimed at treating the somatic dysfunctions. Techniques chosen for the present study are balanced ligamentous/membranous tension techniques [15]. The whole session will last 30 minutes: 10 minutes for evaluation and 20 minutes for treatment [15].

OMT will be performed by registered osteopaths with experience in the neonatology field (OMT group A) and final-year students (OMT group B). Newborns allocated to the study group will undergo osteopathic care in addition to usual care.

The sham group will receive only ‘soft touch’, for 30 minutes, plus routine care, whereas the control group will receive routine care only.

Osteopathic care and sham therapy will be administered once a week according to the treatment group. OMT groups A and B will enter the NICU on different days of the week.

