### Outcomes

Primary outcome will be the mean difference in baseline score changes of PIPP questionnaire between discharge and entry among the three groups.

Secondary outcomes will include:mean difference in PIPP questionnaire scores before and after each treatmentmean difference in LOS measured in days between the three groupsmean difference in costs between the three groupsmean difference in PIPP questionnaire scores between the two OMT subgroupsmean difference in LOS measured in days between the two OMT subgroupsmean difference in costs between the two OMT subgroupsdifference in the risk of adverse events and side effects between the three groupsaverage daily weight gain measured in grams

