## Discussion

The present single blinded RCT has been designed to explore potential advantages of OMT in the management of newborns’ pain. Currently, based on a patient-centred need-based approach, this research will be looking at the benefit of OMT rather than the efficacy of a specific technique or a pre-determined protocol. Moreover, it will attempt to confirm the effectiveness of OMT on LOS-shortening using a larger experimental study design and to corroborate the absence of placebo effects in newborns. Furthermore, it will explore potential differences between expert osteopaths and final-year students on the effectiveness of OMT.

To date, no osteopathic trial has been carried out in this field attempting to quantify the benefits of OMT in newborns’ pain using rigorous procedures and ‘gold-standard’ methods for clinical trials. This will be the first concrete experimental trial addressing this outcome. The expected advantages from the present trial will be reduction of pain, shorter LOS and lower neonatal costs in the OMT groups compared to sham and control groups.

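### The abstract names per-protocol only, while the statistics section names per-protocol and intention-to-treat as joint primary analyses; a superiority trial needs intention-to-treat as its single primary set

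*Protocol article*

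**What the plan says.** The abstract (Methods/design paragraph) states, for all analyses and without mentioning intention-to-treat: "Statistical analyses will use per-protocol analysis method". The Statistical analysis section states: "The primary analysis of the present clinical trial will be conducted according to per-protocol principle and intention-to-treat". It does not rank the two sets, and it does not say whether both must succeed or what follows if they disagree.

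Four other statements bear on the point:

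- **Aim.** The Discussion reads: "The expected advantages from the present trial will be reduction of pain, shorter LOS and lower neonatal costs in the OMT groups", compared with sham and control. This is superiority; no margin is given.
- **Primary outcome.** Outcomes reads: "Primary outcome will be the mean difference in baseline score changes of PIPP questionnaire between discharge and entry among the three groups". Length of stay (LOS) and costs are secondary.
- **Exposure.** The abstract has "Newborns will undergo manual sessions once a week for the entire period of hospitalisation" and Osteopathic procedure has "Osteopathic care and sham therapy will be administered once a week according to the treatment group". The control arm has routine care and no sessions.
- **Cost.** Under Measures, "costs per day are calculated according to local authorities, multiplied by the days of hospitalisation", so cost follows LOS directly.

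**The concern.** Three things are at stake.

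1. A reader cannot tell which analysis is the trial's answer. The abstract leaves out the one set that keeps the randomised comparison intact.
2. The Statistical analysis section, read alone, allows two primary results. If they differ, nothing in the text prevents the more favourable one from being reported as primary.
3. In this design, receiving treatment is tied to an outcome. An infant must stay long enough to meet a weekly visit before having any session, and LOS is an endpoint. Controls have no such hurdle. A per-protocol rule based on sessions received would therefore select on LOS in two arms and not in the third.

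**Working it through.** **Step 1: the plan's own figure.** Inputs from Statistical analysis: f = 0.30, α = 0.05, power 0.80, three groups. For a one-way ANOVA the noncentrality is λ = f² × N.

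- 37 per group: λ = 0.09 × 111 = 9.99, power 0.803 (36 per group gives 0.792). The stated 37 reproduces.
- 40 per group: λ = 0.09 × 120 = 10.8, power 0.836.

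The planned size is therefore sound, and analysing all 40 per group keeps the full power.

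**Step 2: the two statements side by side.**

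| Place | Analysis set | Applies to |
|---|---|---|
| Abstract | per-protocol | statistical analyses in general |
| Statistical analysis | per-protocol and intention-to-treat | the primary analysis |

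These cannot both describe the primary analysis. LOS and cost come under per-protocol only through the abstract's general sentence.

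**Step 3: error rate if either set may count.** Simulation with no true effect: 40 per arm, normal outcome, one-way ANOVA at 0.05 on everyone and again after random exclusions, counting a success if either is significant. The exclusion rates are assumptions.

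| Excluded | Loss in all three arms | Loss in OMT and sham only |
|---|---|---|
| 10% | 0.066 | 0.063 |
| 20% | 0.072 | 0.069 |

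Each test alone stays at about 0.05. The excess comes only from having two chances. Exclusions related to outcome are not covered by this calculation.

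**Step 4: LOS illustration with no true effect.** The documents give neither a per-protocol definition nor any LOS figure, so every input here is assumed: LOS (L) is gamma distributed, the wait to the first visit is uniform over 0 to 7 days, an OMT or sham infant is kept if at least one session occurs before discharge, and all controls are kept.

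- Probability of being kept, given L: w(L) = min(L/7, 1).
- Share lost: 1 − E[w(L)].
- False difference against control: E[L·w(L)] / E[w(L)] − E[L].

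| Mean LOS | Shape 1 | Shape 2 | Shape 3 |
|---|---|---|---|
| 10 days | 28% lost, +3.1 days | 17%, +1.4 | 12%, +0.9 |
| 14 days | 21%, +3.2 | 10%, +1.3 | 6%, +0.7 |
| 28 days | 12%, +3.4 | 3%, +0.8 | 1%, +0.3 |

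With a fixed daily rate, cost shifts by the same proportion: from 0.3/28, about 1%, to 3.1/10, about 31%.

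**Step 5: how far this depends on the assumptions.** Lognormal stays (means 10 to 26 days) with one required session give only about +0.1 to +0.7 days, with false-positive rates for OMT versus control of about 0.05 to 0.07. Requiring two sessions gives +2.0 to +5.5 days. Intention-to-treat stays at about 0.04 to 0.05 throughout.

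**Step 6: direction and contrast.** OMT and sham lose infants by the same mechanism, so OMT versus sham is not biased by it. OMT versus control is, and in the direction of longer OMT stays, against the benefit the Discussion expects.

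**The case against.** The strongest reply is that intention-to-treat is already in the Statistical analysis section, that a journal abstract is condensed, and that a per-protocol definition may exist in a document not shown. On that view only wording is at fault. Part of this stands: the missing definition is not a finding, and the correction is indeed mostly wording. It does not remove the conflict, because the two sentences differ on the page and the fuller one still ranks nothing.

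Three stronger readings are tempting, and the documents do not support them.

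- **That per-protocol does bias LOS here, by a known number of days.** No section defines the set, sets a minimum number of sessions or gives an LOS distribution. The bias can arise; its size cannot be derived. Other exclusions, such as infants with complications, could push the other way.
- **That per-protocol losses would seriously underpower the trial.** That needs losses of about 20 to 25% in all three arms. Under the mechanism above, with 10% lost from OMT and sham only, 36 + 36 + 40 = 112 infants remain, above the 111 from the calculation. Power is about 0.79 to 0.82, depending on the pattern of means.
- **That the transfer criterion is a hidden post-randomisation exclusion.** The words "being transferred to/from other hospital" stand among the eligibility criteria and may refer to a transfer known or planned at screening. Nothing says that a randomised infant transferred later is dropped.

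It is also fair to say that LOS and cost are secondary. For PIPP, the case rests on the contradiction, the missing ranking and the loss of the randomised comparison, not on a calculated bias.

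**Conclusion.** The concern holds in this form. The contradiction and the two unranked primary analyses are on the page and need no assumption. A superiority claim should rest on all randomised infants in the arm assigned. As written, it may rest on a set that gives up that protection, or on whichever of two results is chosen. If either may count, the type I error is about 0.063 to 0.072 instead of 0.05, given 10 to 20% random exclusions.

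For LOS and cost, a per-protocol set that requires at least one session can make OMT look worse than control; OMT versus sham is unaffected by this route. The +0.3 to +3.4 days is an illustration under assumed gamma stays and a uniform wait, not an estimate for this trial.

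**What to change.** In the abstract and the Statistical analysis section, name intention-to-treat (all randomised infants, analysed in the arm assigned) as the single primary analysis for PIPP. Use the same set for LOS, cost and adverse events. Describe per-protocol as a supportive sensitivity analysis that cannot replace the primary result. State that an infant transferred out after randomisation stays in the intention-to-treat set.

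The cost is a few sentences, plus collecting outcome data for infants who miss sessions or leave the unit. The sample size stays at 120. The estimate is slightly diluted: if a tenth of OMT infants have no session and gain nothing from allocation, the expected difference shrinks by about a tenth.

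### Carrying the last PIPP score forward forces the entry-to-discharge change to zero when only the entry score exists, and the planned mixed model makes it unnecessary

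*Protocol article*

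**What the plan says.** The Statistical analysis section of the protocol article states: "Missing data will be handled using the last observation carried forward imputation technique". The Abstract (Methods/design) has the same rule: "Missing data will be handled using last observation carried forward imputation technique". The rule covers all missing data, not only PIPP. It comes without a justification, a missing-data assumption or a sensitivity analysis.

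Four other statements bear on it:

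- **Primary outcome (Outcomes):** "Primary outcome will be the mean difference in baseline score changes of PIPP questionnaire between discharge and entry among the three groups".
- **Model (Statistical analysis):** "A linear mixed effect model will be used to evaluate the PIPP score across groups".
- **Analysis sets (Statistical analysis):** "The primary analysis of the present clinical trial will be conducted according to per-protocol principle and intention-to-treat".
- **Sessions (Osteopathic procedure):** "Osteopathic care and sham therapy will be administered once a week according to the treatment group", "whereas the control group will receive routine care only". A secondary outcome compares PIPP before and after each treatment, so the OMT and sham infants may have scores between entry and discharge. The article describes no such scores for controls.

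**The concern.** The primary outcome is a difference between two scores. If the later one is missing and the earlier one is put in its place, the infant's change is zero by construction. That is harmless only if zero is a fair guess at the unseen change.

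Three consequences follow:

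- Each arm's mean change is pulled toward zero in proportion to its own missingness. A true effect is diluted when missingness is equal, and a false difference appears when it is not.
- The value carried forward may differ in kind between arms. A control may have only the entry score to carry. An OMT or sham infant may have a score taken during the stay, possibly just after a session. The bias can then differ by arm even when the missing shares are the same.
- The filled-in values enter the analysis as if they had been observed, so their uncertainty is ignored.

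The article already plans a linear mixed model. Fitted to the observed scores, it uses incomplete records validly under missing-at-random. Filling the gaps first gives up that advantage.

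**Working it through.** **1. The plan's own figure.** The article states that "the sample size is computed considering an effect size (f) of 0.30, a statistical power of 0.80", with α = 0.05, which gives 37 per group, raised to 40. For a one-way ANOVA with three groups, the noncentrality is λ = N·f². At 37 per group, λ = 111 × 0.09 = 9.99. Power is 0.792 at 36 per group, 0.803 at 37 and 0.836 at 40, so 37 reproduces. The step to 40 covers a loss of 1 − 37/40 = 7.5%. This is the only allowance for loss in the article.

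**2. Formula.** Let D be the true mean change in an arm, m the share with a missing discharge score, and q the fraction of the change already present in the score carried forward. Under LOCF:

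expected arm mean = (1 − m(1 − q))·D

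If the entry score is carried, q = 0 and this becomes (1 − m)·D.

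**3. Assumed inputs.** The article gives no expected change over the stay, no missingness rate and no SD of the change. I take D = −2, −3 or −4, and an SD of change of 3.2. The article gives 3.2 as the SD of a single score under simulated handling. It is also the SD of a change if entry and discharge scores correlate at 0.5, since 3.2 × √(2 × (1 − 0.5)) = 3.2.

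**4. No true effect, unequal missingness, entry score carried.** The false difference is the gap in m times the size of D. For 15% against 5%:

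- D = −2: 0.85 × (−2) − 0.95 × (−2) = −1.7 + 1.9 = 0.2 points
- D = −4: 0.85 × (−4) − 0.95 × (−4) = −3.4 + 3.8 = 0.4 points

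If half of the change had already occurred when the carried score was taken (q = 0.5), these halve to 0.1 and 0.2.

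Type I error of the three-group ANOVA on change scores, 40 per arm, 20,000 simulated trials:

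| Missing by arm | D = −2 | D = −3 | D = −4 |
|---|---|---|---|
| 7.5%, 7.5%, 7.5% | 0.049 | 0.050 | 0.050 |
| 5%, 5%, 15% | 0.059 | 0.071 | 0.085 |
| 5%, 5%, 20% | 0.067 | 0.088 | 0.122 |

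In a milder case (5%, 7.5% and 10% missing, SD 3.1), type I error was about 5.1% for a fall of 2 and 5.7% for a fall of 4.

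**5. True effect, equal missingness.** Take true changes of −4 and −2, a true difference of −2.0, with 7.5% missing in both arms: 0.925 × (−4) − 0.925 × (−2) = −3.70 + 1.85 = −1.85.

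**6. Equal missingness, different scores carried.** Take no true effect, D = −4 and 7.5% missing in each arm. If controls carry the entry score (q = 0), their mean is 0.925 × (−4) = −3.70. If OMT infants carry a mid-stay score with q = 0.5, their mean is (1 − 0.0375) × (−4) = −3.85. The false difference is −0.15, in favour of OMT. If a post-session score lies below the eventual discharge score, q exceeds 1 and LOCF overstates the change.

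**The case against.** The strongest reply is that the inputs are assumed and the harm may be small. The infants are inpatients from entry to discharge, NICU staff acquire medical records daily, and infants transferred to or from other hospitals are excluded. Nothing in the article points to a 5% against 15% split. With equal missingness and no true effect, the test keeps its 5% level. At the 7.5% loss for which the sample size allows, a 2.0-point effect loses only 0.15 points. All of this stands. It limits the size of the problem but does not make zero a better guess at an unseen change.

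Three stronger readings are tempting, and the article does not support them:

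- **A documented fall of 4.0 or 6.9 points.** A reader might take these from the PIPP means in Statistical analysis (10.3 against 6.3, and 12.9 against 6.0) and infer a much larger inflation of type I error. Those gaps are between types of procedure, not between entry and discharge. No expected change over the stay is given. The fall of 4 used above is an assumption and does not rest on them.
- **LOCF always imputes too little change.** That holds when the entry score is carried and PIPP moves steadily. A carried post-session score could overstate the change.
- **Controls always carry the entry score.** This is an inference from their having no sessions. The article does not say that controls are scored only at entry and discharge.

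Nor is the mixed model immune. If missingness depends on the unseen discharge score, an analysis of the observed scores is biased too, hence the sensitivity analysis proposed below.

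**Conclusion.** The point holds at moderate weight. LOCF is a stated choice and the only missing-data rule in the article. It suits an entry-to-discharge change poorly, and the article's own model makes it unnecessary for PIPP.

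The shrinkage to (1 − m)D is exact when the entry score is carried. Its size is not documented. Under the assumptions listed, with one arm at 15% missing against 5% in the others, the false difference is 0.2 to 0.4 points and the three-group type I error about 6% to 8.5%. With equal missingness, type I error stays near 5%, but a true effect is diluted: 2.0 becomes 1.85 at 7.5% missing. When session scores are carried forward, neither the direction nor the equality of the bias across arms is assured.

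A reader might conclude that the primary comparison is invalid as planned. The article does not support that, because the harm depends on how much is missing and how unevenly, and it states neither. The rule should be changed before analysis, but it does not undermine the design or the sample size.

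**What to change.** In Statistical analysis and in the Abstract, replace the LOCF sentence. For PIPP, state that the planned linear mixed model is fitted by REML to all observed scores without imputation, under a missing-at-random assumption. Add one missing-not-at-random sensitivity analysis, for example multiple imputation with a delta shift by arm. Keep LOCF, if at all, only as a further sensitivity analysis.

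The present sentence covers all missing data, so deleting it outright would leave the other outcomes, such as weight gain, without a rule. State separately how missing non-PIPP outcomes are handled.

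The cost is two edited sentences, including the short statement on non-PIPP outcomes, and one extra analysis. The sample size stays at 40 per group.

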### Randomisation and masking

Patients will be randomly assigned in a 1:1:1 ratio to either the OMT, the sham or the control group (Figure 1). Newborns will be eligible for randomisation from the first day of life. Block randomisation will be performed according to a computer-generated randomisation list using a block size of nine, and stratified by OMT group.

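### A single P<0.05 rule is not limited to the primary outcome, while the Discussion sets out to confirm shorter stay, a secondary outcome with no stated error control

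*Protocol article*

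**What the plan says.** - **Outcomes** names one primary outcome, the entry-to-discharge change in PIPP among the three groups. It then lists eight secondary outcomes without ranking them: PIPP around each session; LOS and costs across the three groups; PIPP, LOS and costs between OMT subgroups A and B; adverse events; and daily weight gain.
- **Statistical analysis** describes a regression covering primary and secondary endpoints for A versus B. The next sentence is the only decision rule in the article: "Two-tailed *P*-values of less than 0.05 are considered to indicate statistical difference". It names no endpoint, contrast or family.
- **Methods/design** makes shorter LOS and cost-effectiveness the secondary objectives.
- **Discussion** says of the trial that "it will attempt to confirm the effectiveness of OMT on LOS-shortening using a larger experimental study design". It also lists, beside less pain, the expected advantages of "shorter LOS and lower neonatal costs in the OMT groups compared to sham and control groups".
- **Data entering and data export** contains the only type I error control, a Lan-DeMets version of the O'Brien-Fleming boundary. It sits with the safety review and acts over interim looks, not across endpoints.

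**The concern.** A threshold that is not limited to the primary outcome, together with an announced intention to confirm a secondary effect, leaves nothing in the text that makes the LOS claim depend on the primary result. The trial could find no effect on PIPP, obtain P<0.05 for LOS, and call LOS-shortening confirmed without departing from its protocol.

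The wording also runs the wrong way round. The Abstract, Background and Discussion use the language of exploration for pain, which is the primary question, and the Discussion uses it for experienced osteopaths versus students. It is never used for LOS or costs. The stronger verb is attached to a secondary outcome.

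What is at stake is the evidential status of an LOS result, and to a lesser degree a cost result, after a failed primary.

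**Working it through.** **1. The plan's own figure.** Inputs from Statistical analysis: "the sample size is computed considering an effect size (f) of 0.30", with "a statistical power of 0.80 and an α-level equal to 0.05". There are three groups, allocated 1:1:1 (Randomisation and masking). For a one-way ANOVA F test with n per group, the noncentrality is λ = 3n·f², and power = P[F′(2, 3n−3; λ) > F₀.₉₅(2, 3n−3)].

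| n per group | λ = 3n × 0.09 | Power |
|---|---|---|
| 36 | 9.72 | 0.792 |
| 37 | 9.99 | 0.803 |
| 40 | 10.80 | 0.836 |

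The smallest n reaching 0.80 is 37, as stated. The sample size therefore fits one three-group test at 0.05, and nothing below alters it.

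**2. Chance of at least one false positive for the outcomes the Discussion singles out.** All nulls are taken as true, each test is at two-sided 0.05, and the arms are equal.

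(a) *LOS, one three-group test.* 0.05 by construction.

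(b) *LOS, OMT versus sham and OMT versus control separately.* The two contrasts share the OMT arm, so their correlation is (σ²/n)/(2σ²/n) = 0.5. Simulation (400,000 draws) gives 0.090.

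(c) *LOS and cost, one three-group test each.* If independent, 1 − 0.95² = 0.0975. If the two are the same variable up to a constant, 0.05.

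(d) *LOS and cost, each against sham and against control (four tests).* Simulated over 200,000 null trials. At correlation 1 this reduces to (b).

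| LOS-cost correlation (assumed) | (c) two three-group tests | (d) four pairwise tests |
|---|---|---|
| 0 | 9.75% | 17.2% |
| 0.5 | not tabulated | 16.2% |
| 0.8 | 7.9% | not tabulated |
| 0.9 | 7.1% | 12.6% |
| 0.95 | 6.5% | not tabulated |
| about 1 | 5% | 9.1% |

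**3. Why the correlation is a range.** Measures defines cost as a daily rate multiplied by days in hospital, which puts the correlation near 1. Cost analysis instead uses fixed reimbursements for three DRGs, which loosens the link. The article does not settle which definition supplies the cost outcome, so no single value can be taken from it.

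**4. Which layout applies.** Outcomes speaks of differences between the three groups, which fits (a) or (c). The Discussion states the expected advantages against both sham and control, which fits (b) or (d). The article does not choose.

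**The case against.** The strongest reply is that the criticism reads too much into silence. Ordering or adjusting secondary outcomes is commonly left to the SAP, which is not shown, and a journal article condenses the full protocol. No sentence says the secondaries are unadjusted. With one primary outcome, the number of secondaries does not inflate the primary error rate. The LOS sentence is Discussion narrative and speaks only of an attempt.

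Much of this stands. The missing hierarchy alone would be no finding, and the primary analysis is untouched. That the sample size ignores LOS and cost is normal practice. What remains is in the stated text: a significance rule with no endpoint limit, placed directly after a sentence that covers secondary endpoints, and a declared aim to confirm one of those endpoints.

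Stronger readings are tempting and should be resisted:

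- *A chance secondary result will be reported as confirmation.* The text allows this but does not commit to it. It promises only CONSORT reporting.
- *The trial claims to confirm lower costs.* It says only that lower costs are expected.
- *The error rate of the LOS claim is about one in three.* The figure 1 − 0.95⁸ = 33.7% is the chance of any false positive among eight independent tests. It says nothing about LOS in particular, which stays at 5% under one three-group test.
- *The error is well above 5% on any reading.* The figures in (b) and (d) need separate unadjusted comparisons that Outcomes does not prescribe. Three-group tests of LOS and cost reach only 7.1% at a correlation of 0.9.

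**Conclusion.** The point holds as a modest defect of stated text. The 0.05 rule is not confined to the primary PIPP test, and LOS, a secondary outcome, is put forward for confirmation with no protection described. A failed primary followed by a claim of confirmed LOS benefit is compatible with the document.

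The false-positive chance for the outcomes concerned is:

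- 5% for one three-group LOS test;
- about 9% for LOS against sham and control separately;
- about 5-10% for three-group tests of LOS and cost;
- about 9-17% for LOS and cost each against both comparators.

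These figures assume that all nulls are true, arms are equal, test statistics are approximately normal, and the LOS-cost correlation lies between 0 and 1. Even at the 5% end, the claim would be made without regard to whether the primary succeeded. The primary test's error rate and the 37 (raised to 40) per group are not in question.

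**What to change.** Amend Statistical analysis and one sentence of the Discussion before outcome data are analysed.

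**Simplest version.** Restrict the two-tailed 0.05 decision rule to the primary PIPP test. Report the secondary outcomes, all A-versus-B comparisons and the effects stratified by gestational age as exploratory estimates with 95% CI and no claim of significance. In the Discussion, replace the verb *confirm* with *explore* for LOS.

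**If a confirmatory LOS claim is wanted.** Test LOS at two-sided 0.05 only after the primary PIPP test succeeds, in a fixed order: OMT versus sham, then OMT versus control, stopping at the first non-significant result. The text should say which primary result opens this step. The other secondaries stay exploratory.

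In either version, keep adverse events outside any hierarchy so that a harm signal is not suppressed.

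The cost is a few sentences, with no extra infants or data. The price is that a favourable LOS or cost result after a failed primary can no longer be called confirmed.
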